### Primary outcome

The primary endpoints of the study are HbA1c and antidiabetic medication dosage. These primary endpoints will be combined to compare the total successful outcomes between the FMD group and the control group after 12 months of follow up. A successful outcome will be defined as any reduction in the antidiabetic medication dosage and/or a decrease of HbA1c of 5 mmol/mol or more. HbA1c and antidiabetic medication dosage will also be recorded after 6 months.

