### Baseline data

Baseline data from the two groups will be compared on the following baseline values: age, gender, BMI and metabolic parameters. The values will be summarized using mean and standard deviation, or in case of an asymmetric distribution, by using median and interquartile range.

Hypothesis tests will be carried out using t-tests for independent samples, or, if the assumption of normality is violated, with a Mann-Whitney test. Multiple testing will be corrected for by using the Benjamini-Hochberg procedure. If the groups are found to be imbalanced on one or more covariates, then the following analyses will be adjusted for those covariates. Furthermore, the following analyses will be adjusted for gender and for weight < 100 kg or > 100 kg, since randomization is stratified for these values.

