### Primary and secondary outcomes

Primary and secondary outcomes will be summarized using mean and standard deviation, or in case of an asymmetric distribution, by using median and interquartile range. HbA1c and antidiabetic medication dosage will be compared between the two groups, using t-tests for independent samples, or, if the assumption of normality is violated, with a Mann-Whitney U test. The values at 12 months will be used for these tests.

To compare the total successful outcomes, the primary endpoints HbA1c and antidiabetic medication dosage will be combined. A successful outcome will be defined as any reduction in the antidiabetic medication dosage and/or a decrease of HbA1c of 5 mmol/mol or more. This will be compared between the two groups as described above. To correct for multiple testing, the procedure of Benjamini-Hochberg will be used.

To detect a difference in the profiles of the outcomes that are measured repeatedly during the course of the study, a mixed model will be used. This model can be used if there is missing data, and if participants have their visits at different time points. The interaction between time and treatment arm will be included. Besides a random slope per participant, a random intercept and the inclusion of splines will be considered. In case complete observations are available for at least 80% of the participants, and if the pattern of missing observations is deemed noninformative, the mixed model will be compared to a generalized least squares model with unstructured, compound symmetry, or AR (1) covariance structures. The choice between the options will be made using the AIC criterion.

As multiple primary endpoints are measured repeatedly, multiple mixed models will be fit. For each of the models, the outcome of the global F or LR test (where appropriate) will be reported, and significance evaluated using the procedure of Benjamini-Hochberg.

The secondary outcome ‘feasibility in practice’, measured as the percentage of compliant participants, will not be tested, as there is no reference value for comparison.

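### The significance rule for the repeated-measures models does not limit the global F or likelihood-ratio test to the treatment terms; in the whole-model sense it can be significant with no treatment effect

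*Protocol article*

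**What the plan says.** All references are to the protocol article.

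- **Purpose of the models** (Primary and secondary outcomes): "To detect a difference in the profiles of the outcomes that are measured repeatedly during the course of the study", a mixed model is used, with a generalised least squares model as a conditional alternative.
- **Treatment term** (same section): "The interaction between time and treatment arm will be included". The interaction is put in the model but is not named as the hypothesis to be tested.
- **Outcomes concerned** (same section): "As multiple primary endpoints are measured repeatedly, multiple mixed models will be fit". The Primary outcome section adds that "HbA1c and antidiabetic medication dosage will also be recorded after 6 months", and Table 2 lists both at baseline, 6 and 12 months.
- **Significance rule** (same section): for each model, "the outcome of the global F or LR test (where appropriate) will be reported, and significance evaluated using the procedure of Benjamini-Hochberg". Neither the tested terms nor the reduced model is given.
- **Other terms in the models** (Baseline data): "the following analyses will be adjusted for gender and for weight < 100 kg or > 100 kg", and "If the groups are found to be imbalanced on one or more covariates, then the following analyses will be adjusted for those covariates".

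The same section separately compares HbA1c and medication dosage at 12 months by t-test or Mann-Whitney test, and compares the combined success endpoint. Those comparisons do not use the global test.

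**The concern.** A global F or likelihood-ratio test of a fitted model usually compares the full model with one that has no explanatory terms. Here the full model holds time, arm, arm-by-time, gender, weight stratum and possibly more. Such a test answers whether anything in the model predicts the outcome. The trial asks whether the arms differ.

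A change common to both arms is plausible, because under Usual care the GP may adapt medication towards an HbA1c target in either arm. Body weight stratum or gender may also be related to HbA1c or dosage. Either would make a whole-model test significant without any effect of the diet. Benjamini-Hochberg cannot repair this, because it controls errors across the p-values it is given and these p-values would not be about treatment.

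The article calls for adjusted analyses, and the t-test and Mann-Whitney test cannot adjust for covariates. Of the named between-arm methods for HbA1c and dosage, the repeated-measures models are therefore the ones that can supply the adjusted comparison. Two analysts following the text could report opposite conclusions from the same fitted model.

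**Working it through.** **1. The plan's own figure.** The article gives no figure for the repeated-measures test. Its one power figure is for the binary composite: 5% against 26%, 45 per arm, two-sided 5%, 80% power. With the pooled normal approximation, the mean rate is (0.05 + 0.26)/2 = 0.155 and

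z = [0.21 × √45 − 1.96 × √(2 × 0.155 × 0.845)] / √(0.05 × 0.95 + 0.26 × 0.74) = (1.409 − 1.003)/0.490 = 0.828,

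which gives 79.6% power. The figure is reproduced and does not depend on the global test.

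**2. Inputs for the check.**
- From the article: 45 analysed per arm (N = 90), three time points (T = 3), 5% significance level, and a model with time, arm, arm-by-time, gender and weight stratum.
- Assumed, because the article gives none: a normal outcome with total SD 1, a random intercept with within-person correlation ρ of 0.4, 0.6 or 0.8, complete data, gender and weight stratum each split about evenly, and a linear change common to both arms of 0 to 0.5 SD over 12 months. Some settings add a weight-stratum difference.
- The true treatment effect is zero throughout.

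**3. Tests compared.** All are maximum-likelihood ratio tests. With balanced data,

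LR = N ln(B_reduced/B_full) + N(T − 1) ln(W_reduced/W_full),

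where B is the residual sum of squares of the participant means and W that of the within-person contrasts. Degrees of freedom:
- whole model: arm 1 + gender 1 + weight 1 + time 2 + arm-by-time 2 = 7
- arm-by-time only: 2
- arm plus arm-by-time: 3

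**4. Results.** Rejection rates (%) with no treatment effect, 4,000 runs per setting:

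| Common change (SD) | Weight-stratum effect (SD) | ρ | Whole model | Arm-by-time | Arm + arm-by-time |
|---|---|---|---|---|---|
| 0 | 0 | 0.6 | 6.1 | 5.4 | 5.9 |
| 0.1 | 0 | 0.6 | 10.4 | 5.3 | 5.7 |
| 0.2 | 0 | 0.6 | 30.6 | 5.4 | 5.9 |
| 0.3 | 0 | 0.6 | 62.3 | 5.3 | 5.9 |
| 0.5 | 0 | 0.6 | 98.7 | 5.6 | 6.3 |
| 0 | 0.3 | 0.6 | 17.5 | 5.1 | 6.1 |
| 0 | 0.5 | 0.6 | 47.4 | 5.1 | 4.9 |
| 0.3 | 0.3 | 0.6 | 74.9 | 5.5 | 6.2 |
| 0.3 | 0 | 0.4 | 42.8 | 5.1 | 4.9 |
| 0.3 | 0 | 0.8 | 92.3 | 4.8 | 5.0 |
| 0.3 | 0.3 | 0.8 | 95.0 | 6.1 | 6.6 |

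The slight excess over 5% in the treatment tests comes from the chi-square approximation and simulation error.

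**5. Check by formula.** A common linear change δ over three equally spaced visits gives the whole-model test a noncentrality of Nδ²/[2(1 − ρ)]. For δ = 0.3 and ρ = 0.6 this is 90 × 0.09/(2 × 0.4) = 10.1. A chi-square variable with 7 df and that noncentrality exceeds the 5% critical value of 14.07 with probability 62.1%, against 62.3% simulated.

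**6. Check with the other model form.** This used generalised least squares with unstructured covariance, an assumed SD of 10 mmol/mol and ρ = 0.7. The 7-df whole-model F test rejected in 4.8%, 36.3%, 73.9% and 96.0% of null trials for a common drift of 0, 2, 3 and 4 mmol/mol. The 2-df arm-by-time test stayed at 4.6% to 5.2%.

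**The case against.** The strongest reply is that the article never says the test covers time and covariates. Its aim is to detect a difference in profiles, and the interaction is in the model. With categorical or splined time, the interaction has several coefficients, and one joint test of them can fairly be called global as opposed to visit-by-visit tests. That test is valid. This stands: a reader might infer that the plan is committed to an invalid test, and the text does not support that.

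Three further inferences are not supported either.
- **That 12 months is left untested.** The same section compares HbA1c and dosage at 12 months, and the powered composite has its own comparison.
- **That a spurious result here loosens the Benjamini-Hochberg thresholds elsewhere.** The procedure is mentioned separately for the 12-month comparisons and for the mixed models, and nothing says the two families are pooled.
- **That a common drift of a given size is expected.** The article gives no drift, SD or correlation. With no drift and no covariate effect, even the whole-model test is close to 5%. Medication dosage was not simulated.

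It may also be said that the tested contrast belongs in the SAP. That would answer a silent article. This one states the test and the multiplicity procedure that decide significance, and the test it names has an ordinary meaning that does not answer the trial's question.

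**Conclusion.** The point holds as a defect in a stated decision rule: the hypothesis tested by the global F or likelihood-ratio test is not fixed, and its ordinary whole-model reading is invalid for judging treatment. On that reading, the chance of a significant result with no treatment effect runs from 10.4% to 98.7% for a common 12-month change of 0.1 to 0.5 SD at correlation 0.6. At a change of 0.3 SD it is 42.8% at correlation 0.4 and 92.3% at 0.8. On the arm-by-time reading it is 4.8% to 6.1%, whatever the common change or covariate effect. The sizes rest on the assumed change, correlation and normal outcome; the direction does not depend on any one of these values.

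The scope is the repeated-measures models only. It should be corrected before analysis, but it does not touch the separate 12-month tests or the power calculation.

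**What to change.** In Primary and secondary outcomes, replace the global test with wording to this effect: for each repeated-measures model, significance is judged on the joint F or likelihood-ratio test of the arm-by-time terms, against a reduced model that keeps time, arm, gender, weight stratum and any other covariates. If arm plus arm-by-time is preferred, say so in advance; the reduced model then drops arm as well and keeps time and all covariates. Both versions hold close to 5% in the check above.

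Enter only these p-values into Benjamini-Hochberg for these models. For each endpoint, report the model-based arm difference at 12 months with its 95% CI.

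The cost is a sentence or two of plan wording. The full model is unchanged, and no further data or participants are needed.

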### Cost-effectiveness analysis

The economic evaluation will consist of both a trial-based cost-effectiveness analysis with a time horizon of 1 year and a model-based cost-utility analysis with a lifetime horizon.

In the trial-based economic evaluation, the effects of the FMD will be compared to usual care and related to the difference in costs. Differences in mean costs and effects (HbA1c -level and QALYs) between strategies will be compared with two-sided bootstrapping. In a net-benefit analysis, costs will be related to the participant reported outcomes and presented in a cost-effectiveness acceptability curve. No discounting will be applied due to the time horizon of the economic evaluation of 1 year. Multiple imputation will be used for handling missing data. The evaluation will be performed from a healthcare and societal perspective. Sensitivity analysis will be carried out for the most important assumptions.

In the model-based cost-utility analysis the UKPDS Outcomes model will be used to estimate lifetime costs and QALYs for the FMD in comparison to usual care [32]. In this lifetime cost-utility analysis costs will be discounted at a percentage of 4% and effects at a percentage of 1.5%, according to the Dutch guidelines for health economic research [33]. Sensitivity analysis will be carried out for the most important input parameters.

Costs consist of healthcare costs and non-healthcare costs, such as costs of food (cost of the FMD and usual diet) and productivity costs (absence of paid and unpaid work). Healthcare costs concerns the costs of health care use related to diabetes during the year of follow-up e.g. GP visits, visits to dietician, medication. Costs of the FMD will be based on the putative market price. Health care use and absence from work will be assessed with the cost questionnaire (see Table 2). For the valuation of health care, standard prices published in the Dutch costing guidelines will be used [34]. Costs of absenteeism from paid work will be calculated using the friction cost method. Quality-of-life adjusted life-years (QALYs) will be estimated with aid of the EQ-5D-5L. Utilities will be calculated from the EQ-5D-5L questionnaire using the Dutch tariff [35]. Using the area-under-the-curve method for the utility scores obtained for each participant, the QALY outcome per participant will be obtained for the trial-based cost-effectiveness analysis. Furthermore, utility values will be used as input in the model for the lifetime cost-effectiveness analysis.

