### Intervention

Participants will be randomised to receive the FMD for 5 consecutive days a month during a year plus usual care or usual care only. The use of metformin will be continued during the study, including the FMD periods.

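### The FMD's price is classed as a non-healthcare food cost, so on a direct reading the healthcare-perspective comparison leaves it out

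*Protocol article*

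**What the plan says.** All the relevant text is in the Protocol article, mostly under Cost-effectiveness analysis.

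- **Perspectives.** For the trial-based evaluation: "The evaluation will be performed from a healthcare and societal perspective".
- **Cost categories.** "Costs consist of healthcare costs and non-healthcare costs, such as costs of food (cost of the FMD and usual diet) and productivity costs". The FMD is paired with the usual diet as a food item, beside productivity costs.
- **Healthcare costs.** "Healthcare costs concerns the costs of health care use related to diabetes during the year of follow-up e.g. GP visits, visits to dietician, medication". The FMD is not among the examples.
- **Valuation.** "Costs of the FMD will be based on the putative market price". No amount is given, and nothing says who would pay.
- **Comparison.** In the trial-based evaluation, "the effects of the FMD will be compared to usual care and related to the difference in costs".
- **Quantity.** Under Intervention: "Participants will be randomised to receive the FMD for 5 consecutive days a month during a year plus usual care or usual care only".

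Sensitivity analyses are promised for the main assumptions of the trial-based evaluation and the main inputs of the lifetime model. The lifetime model has no separate statement of perspective and no rule on the FMD's price.

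**The concern.** The FMD is the only planned difference between the arms. A cost comparison of the arms should therefore contain both what the FMD costs and what it changes elsewhere. If the healthcare perspective takes only the items defined as healthcare costs, it contains the second part without the first. Any reduction in medication or visits would be credited to the FMD, any increase would be charged to it, and its purchase price would appear nowhere in that perspective.

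The omission runs in one direction. It lowers the FMD's incremental cost, raises its net benefit and shifts the acceptability curve in its favour. The planned sensitivity analysis would not reveal this, because varying the price of an item that is not in the sum leaves the sum unchanged.

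**Working it through.** The article states no cost result, so there is no figure to reproduce. The check maps the listed cost items to the two perspectives and then sizes the gap.

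**Step 1: which category holds the FMD.** In the sentence that lists the categories, the examples introduced by *such as* include productivity costs, which are not healthcare costs. The examples therefore illustrate the non-healthcare category, and the FMD is one of them. The following sentence confines healthcare costs to diabetes-related care use.

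**Step 2: mapping.** This step is an inference, since the article does not state which categories enter which perspective.

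| Item | Healthcare | Societal |
|---|---|---|
| GP, dietician, medication and other diabetes care | yes | yes |
| Price of the FMD | no | yes |
| Usual diet | no | yes |
| Productivity | no | yes |

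**Step 3: the gap.** Let ΔH be the difference in diabetes-related care costs (FMD minus usual care), k the number of cycles supplied per participant, and P the price of one 5-day cycle.

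- Healthcare incremental cost, direct reading: ΔH
- Healthcare incremental cost with the FMD counted: ΔH + kP
- Difference: kP

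Monthly cycles for a year give k = 12 for a fully supplied participant, so the gap is 12P. Participants who receive fewer cycles contribute less. The trial-based evaluation applies no discounting ("No discounting will be applied due to the time horizon of the economic evaluation of 1 year"), so the sum needs no further adjustment.

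**Step 4: illustration.** P is assumed; the article gives no price.

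| Assumed P (euro) | 12P (euro per participant) |
|---|---|
| 50 | 600 |
| 100 | 1,200 |
| 150 | 1,800 |
| 200 | 2,400 |
| 250 | 3,000 |

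On the direct reading the corresponding entry in the healthcare perspective is 0 in every row.

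**Step 5: on the QALY scale.** Net benefit at a threshold λ is overstated by 12P/λ QALY. The thresholds are also assumed.

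- P = 100, λ = 50,000: 1,200 / 50,000 = 0.024
- P = 100, λ = 20,000: 1,200 / 20,000 = 0.06
- P = 250, λ = 20,000: 3,000 / 20,000 = 0.15

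**Step 6: when the conclusion would change.** Dominance requires both lower cost and better effect. Omitting the price creates an apparent saving where none exists only if ΔH < 0 and ΔH + 12P > 0, that is, when the saving in care costs lies between 0 and 12P. Outside that range the sign of the cost difference is the same with or without the FMD, although its size is still off by 12P.

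**Step 7: sensitivity analysis.** On the direct reading the healthcare incremental cost is ΔH, which does not contain P. Changing P moves only the societal result.

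**The case against.** The strongest objection is that the omission is inferred. No sentence says that the healthcare perspective uses healthcare costs alone. The list of healthcare items is open-ended, the FMD has its own valuation sentence, and the comparison of effects with costs excludes nothing explicitly. An article also condenses, and a full allocation of cost items to perspectives may well sit in a fuller plan that is not shown. What stands is that the zero price is a reading and not a declared rule. It does not remove the point, because the article does more than stay silent: it places the FMD in the non-healthcare category and defines the healthcare category without it.

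A second objection is that the FMD is a packaged food. If patients would buy it themselves, leaving it out of a payer's account is coherent. That is possible, but the article neither says who pays nor gives this as its reason.

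A reader might also infer more than the text supports:

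- *The healthcare-perspective result is wrong by construction.* Without a stated mapping, and with a patient-pays reading open, this is too strong.
- *Any saving or QALY gain would make the FMD look dominant.* This does not follow. A saving with a QALY loss is not dominance, nor is a QALY gain with greater care use, and extra visits or drugs in the FMD arm would still be counted.
- *The lifetime model omits the price as well.* The article shows no such omission; it simply does not say.
- *The euro and QALY amounts measure the bias.* They rest on assumed prices and thresholds. The documents support only 12 times an unknown price.

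**Conclusion.** The point holds in a limited form. On the direct reading of the article's own definitions, the healthcare-perspective comparison includes the FMD's effects on diabetes care costs but not its acquisition price. Incremental cost is then understated by about 12P for each fully supplied participant, with P unstated. This rests on two readings: that the healthcare perspective takes the healthcare category as defined, and that one cycle a month for a year means 12 cycles.

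The defect is confined to one of two perspectives in a secondary outcome. The societal analysis includes the price. Whether the lifetime model is affected cannot be determined from the article. It is worth correcting before analysis because the direction of the error is known and the planned sensitivity analysis on price would not expose it.

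**What to change.** 1. Count the FMD as an intervention cost in the healthcare perspective as well as the societal one, at the market price already planned and by the number of cycles each participant actually used.
2. If a result without the price is wanted, present it only as a labelled scenario in which the patient pays, with that assumption stated.
3. State whether the lifetime model includes the FMD's price.

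One cost item that the plan already prices is added to a second perspective, so no new data are needed. Varying that price in the planned sensitivity analysis would then affect both perspectives. The downside is a less favourable healthcare-perspective result for the FMD.

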### Secondary outcomes

Bodyweight, waist circumference, body mass index and body fat percentage: recorded at baseline and every following study visit.Blood pressure: systolic and diastolic values measured at baseline and every following study visit.Fasting glucose: measured at baseline, after 6 months and after 12 months.Glucose and insulin response to an oral glucose load: OGTT measured at baseline, after 6 months and after 12 months.Plasma lipid profiles: measured at baseline, after 6 months and after 12 months.Metabolomics: measured at baseline and after 12 months.High sensitive CRP: measured at baseline, after 6 months and after 12 months.Dosage of statins and antihypertensive medication: recorded at baseline, after 6 months and after 12 months.Visceral fat, liver/heart ectopic fat, total body fat: from magnetic resonance imaging, measured at baseline, after 6 months and after 12 months.Cardiovascular function: from magnetic resonance imaging, measured at baseline, after 6 months and after 12 months.Gut microbiota architecture: measured from stool samples stored at baseline, after 1 week, after 6 months and after 12 months.Change in dietary pattern: DHD-FFQ measured at baseline, after 6 months and after 12 months [25].Cost-effectiveness analysis: The economic evaluation will consist of both a trial-based cost-effectiveness analysis with a time horizon of 12 months and a model-based cost-utility analysis with a lifetime horizon.Change in physical activity: SQUASH measured at baseline, after 6 months and after 12 months [26].Quality of life: EQ-5D-5L measured at baseline, after 3 months, after 6 months, after 9 months and after 12 months [27, 28].Treatment satisfaction: DTSQs at baseline, after 3 months, after 6 months, after 9 months and after 12 months [29]. DTSQc after 12 months [30].Feasibility in clinical practice: Percentage of fully compliant participants after 12 months, where compliance is based on self-report and laboratory measures. Glucose levels and finger-stick ketone bodies tests are performed after several FMD periods.

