### Safety

#### Adverse events

Previous experience with this FMD did not reveal serious side effects. Some weakness and headache were sometimes reported. Very few participants dropped out of previous studies because of physical side effects [20, 21]. Hypoglycaemia is not very likely to occur when participants use the FMD while also using metformin, since metformin has no effect on insulin secretion. Metformin will therefore be continued during the FMD. GPs are asked to inform the research team about Serious Adverse Events (SAEs) and Adverse Events (AEs). Participants will be asked at every visit about SAE’s. AE’s will be recorded at several study visits (see Table 2) and during telephone contacts with the research team.

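### Healthcare costs limited to diabetes-related care, and productivity costs limited to absence, are narrower than the healthcare and societal perspectives that the plan states

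*Protocol article*

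**What the plan says.** The section Cost-effectiveness analysis of the protocol article sets the viewpoint without qualification: "The evaluation will be performed from a healthcare and societal perspective". It then defines what is counted. For healthcare: "Healthcare costs concerns the costs of health care use related to diabetes during the year of follow-up", with visits to the GP and the dietician and medication as examples. For the rest: "non-healthcare costs, such as costs of food (cost of the FMD and usual diet) and productivity costs (absence of paid and unpaid work", where the bracket closes. On the diet itself: "Costs of the FMD will be based on the putative market price".

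The cost questionnaire is said to capture health care use and work absence; that sentence does not repeat the limit to diabetes. Table 2 schedules it at T3, T4, T6 and T8. Absence from paid work is valued by the friction cost method. QALYs are the area under each participant's EQ-5D-5L utility curve. Sensitivity analyses are promised for the main assumptions, without naming them.

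Two other sections bear on the point. Secondary outcomes lists: "Dosage of statins and antihypertensive medication: recorded at baseline, after 6 months and after 12 months". Adverse events says of earlier experience with this diet: "Some weakness and headache were sometimes reported".

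**The concern.** A perspective is a commitment about whose costs count. Here the cost definition is narrower than the commitment, and the narrowing need not affect the arms equally.

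Only one arm receives the diet. A GP visit for a diet-related headache is, on a literal reading, not diabetes care, so it would be dropped, and dropped mainly in the FMD arm. The loss of quality of life from the same headache is not filtered in this way: the EQ-5D-5L is not specific to diabetes, so whatever is present when it is completed enters the QALYs. Costs and effects then have different scopes.

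The limit also requires someone to decide which care was for diabetes. Participants know their allocation, and use of care comes from a questionnaire, so that decision rests on unblinded reports.

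At stake is the cost difference between the arms in the trial-based economic evaluation, and the claim that it represents the two stated perspectives. The primary endpoint is not affected.

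**Working it through.** The plan states no figure for this point, so the check sets each cost item against the text.

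| Cost item | What the article says | Status |
|---|---|---|
| The diet | Included, at a putative market price | Counted |
| Usual-diet food | Included | Counted |
| Absence from paid and unpaid work | Included, with no limit by cause | Counted, also when the diet causes it |
| Diabetes-related GP and dietician visits and medication | Named as examples | Counted |
| Care for side effects of the diet | Not mentioned; only diabetes-related use is counted | Out on a literal reading |
| Statins and antihypertensives | Medication is listed without restriction to glucose-lowering drugs, but under the diabetes limit; doses are recorded | Undetermined |
| Reduced output while at work | Not mentioned; the bracket after productivity costs gives absence | Not counted |

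**Direction.** Write the true cost difference as ΔC = C(FMD) − C(usual care). If items are omitted, the estimate is ΔC − [omitted(FMD) − omitted(usual care)].

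- Side-effect care arises mainly in the FMD arm, so the bracket is positive for that item and ΔC comes out too low.
- Reduced output acts the same way if output falls on diet days.
- If statin or antihypertensive doses fall more in the FMD arm and are not costed, the bracket is negative for that item and ΔC comes out too high.

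The terms can have opposite signs, so the net direction is unknown.

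**Size.** The documents support one quantity: 5 days × 12 months = 60 diet days a year if all cycles are completed, or 60 × 5/7 = 42.9 working days for a full-time worker. Everything beyond that must be assumed. For reduced output alone, assume that 30–70% of participants work, that output falls by 5–20% on those days, and that a working day is worth EUR 280 (8 h × EUR 35):

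- low: 42.9 × 0.3 × 0.05 = 0.64 days; × 280 = about EUR 180
- high: 42.9 × 0.7 × 0.20 = 6.0 days; × 280 = about EUR 1,680

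The range is about ninefold (6.0 / 0.64). None of the three assumed inputs comes from the documents, so this shows only how strongly an answer would depend on them.

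**The case against.** The case for leaving the definition alone has real content.

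- **The diet is being tested as a diabetes treatment,** so care for its side effects could be read as diabetes-related. That reading is possible, but the article does not adopt it, and two analysts could differ.
- **The lists are illustrative** ('e.g.', 'such as'). This is true of the items. It does not loosen the diabetes limit or the bracket that explains productivity costs.
- **Costing only disease-related care is a recognised trade-off against noise,** and there are only 50 participants per arm. This stands, and it is why all-cause costing belongs in a sensitivity analysis here and need not be the base case.
- **The diet was reported as well tolerated,** with no serious side effects in earlier use. This stands too: side-effect care may be small.
- **The questionnaire and the full economic plan are not shown.** Details of attribution may be in them. The scope of costs, however, is stated in the article, and it does not match the stated perspectives.
- **Sensitivity analyses are already promised.** Their scope is open, and they cannot recover output losses that were never collected.

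Some stronger readings are tempting but not supported. A reader might infer that the costs caused by the diet are left out in general; its price, food costs and absence from work are in. A reader might infer that savings on statins and antihypertensives are excluded; the text is ambiguous on this and does not exclude them. A reader might also conclude that neither perspective is delivered at all, which goes too far given what is counted.

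**Conclusion.** The point holds as a mismatch of scope. Healthcare costs limited to diabetes-related care, and productivity costs limited to absence, are narrower than the healthcare and societal perspectives stated in the same section. On a literal reading, side-effect care is omitted from incremental costs, mainly in the FMD arm, while its effect on quality of life can still reach the QALYs. Reduced output at work is not counted. The status of cardiovascular medication needs to be stated.

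The size and net direction of any bias cannot be computed from the documents. The EUR 180–1,680 illustration covers one component, assumes that all cycles are completed and that output falls on every working diet day with no loss in controls, and should not be cited as an estimate.

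The conclusion assumes that the definition is applied as written. If the full economic plan already counts side-effect care and cardiovascular drugs, what remains is to align the article's wording and to address output at work. This concerns a secondary, economic analysis, but it is worth correcting because most of the correction is cheap.

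**What to change.** In the section Cost-effectiveness analysis:

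1. Define healthcare costs as diabetes care plus care for adverse events plus statin and antihypertensive medication. The doses of these drugs are already recorded at baseline, 6 and 12 months. Take adverse-event care from the cost questionnaire in both arms alike, because the telephone calls at which adverse events are also noted are described for the FMD group.
2. Add a named sensitivity analysis that values all health care use reported in the cost questionnaire, whatever its attributed cause. This assumes that the questionnaire asks about health care use without a diabetes limit, as the article's sentence suggests; if it does not, say so as a limitation.
3. For reduced output at work, choose one of two routes. Either run a scenario analysis, using an item asked identically in both arms at the remaining visits if feasible, or describe the societal perspective as limited to absence-based productivity costs. An item restricted to diet days would have no equivalent in the control arm. Because the trial was under way at publication and follow-up was expected to end in June 2021, a new item would also miss periods already completed.

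The cost is slightly more costing work, and wider intervals for the cost difference in the all-cause analysis. Steps 1 and 2 need no new data collection if the questionnaire already covers all health care use.
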